**Figure 1 Fig1:**
[figure not shown]
**Flowchart of study.**

### Intervention design

After randomisation, researchers will conduct focus group discussions with parents, Stage 3 (year 5 and 6) students, and individual interviews with teachers. This qualitative research will aim to investigate the results of the baseline data collection and inform the intervention design with these schools. These focus groups and interviews will unpack the positive and negative aspects of the school’s utilisation of sun-safe hats, sunscreen and staff role modelling of sun-safe behaviours.

Interviews and focus groups will also investigate schools’ understanding of being ‘SunSmart’ and other aspects of the existing school sun protection policy; including sun-safe school uniforms, the provision of shade, scheduling of outdoor activities, sun protection within the school curriculum and finally, inclusion of the local community into school sun-safe practices. This broader context will allow analysis of the relative importance of the three specific study outcomes and other factors that may have influenced the baseline results.

Data from this formative research will be analysed using coding and intra and inter-textual analysis to ascertain common themes across schools [16]. Formative interview data will be utilised to refine the design and enactment of the intervention.

The intervention development and implementation will be based on Social Cognitive Theory (SCT) [17] which focuses on the interplay between personal, behavioural, and environmental factors. The personal factors identified in SCT (such as the thoughts, emotions and biological dispositions of an individual) will be addressed by the intervention program by influencing the value systems that may reinforce the low emphasis on the school sun protection policy. The nuanced behavioural factors associated with sun protection behaviours, such as the wearing of hats and sunscreen and playing in shaded areas also need to be identified objectively and addressed within the intervention program. Finally, the environmental factors (both social and physical) that often exist beyond the immediate control of individual schools need to be identified and addressed in order to remove potential barriers and to provide opportunities for social support. An example of influencing this factor may include the utilising and modifying of existing school infrastructures that were not used by the school in order to make them more accommodating for the sun-safe practices without any additional financial outlay.

The intervention will also be based on the key principles of the WHO Health Promoting Schools (HPS) Framework [18] that focuses on the connection between formal curriculum, school ethos and the school-home-community partnership. By addressing these overlapping and interconnecting components, schools are more likely to provide comprehensive and effective health promotion throughout the entire school community. The formal curriculum of the HPS framework refers to the teaching and learning programs provided by the school, and advocates these be distributed in a variety of subjects and classes rather than just traditional health education classes [19]. A school ethos is derived by the components put in place which construct its values and atmosphere, including organisation, environment, policies and procedures [19]. The partnership between the school and local community is a vital component for school health promotion. By incorporating families and the community into the life of the school, a supportive learning and healthy environment can be established [19].

In collaboration with CCNSW and each of the primary schools assigned to the intervention group, a policy driven intervention will be rolled out over the course of two school terms (June-December 2015). Post-test data will be collected during the latter half (October-December 2015) of the intervention implementation with follow-up data collected after the schools return from summer break between January and April 2016.

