**Methods/Design:**

Data will be collected in the summer months of 2014, 2015, and 2016 as part of an 18-month cluster-controlled trial in NSW primary schools (n = 20). Researchers will conduct three direct observations to record students’ hat use and teachers’ use of sun protective measures during recess and lunch periods in each school. Researchers will also record the volume of sunscreen that the Year 6 classes in each school utilise over the term. At the conclusion of baseline data collection, five schools will be randomised into an intervention group that will work with researchers to develop a policy-driven intervention to improve sun safety behaviour in NSW primary schools.

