### Wearing of headwear and prevailing environmental conditions

The primary outcome will be children’s wearing of a sun protective headwear during break periods of the school day (i.e. recess and lunch). Currently no direct observation instruments to record sun-safe behaviours of children in school settings exist. However several direct observation tools of physical activity do exist, and one of these will be adapted to capture sun-safe behaviour data in children. The System for Observing Play and Recreation in Communities (SOPARC) is based on momentary time sampling techniques in which systematic and periodic scans of individuals and contextual factors within predetermined target areas are made [20]. iPad tablets (Apple Inc, USA) installed with the iSOPARC Application Version 1.75 (CIAFEL, Portugal: http://ciafel.fade.up.pt) will be used to provide an objective measure of the wearing of hats by children during recess and lunch.

During a scan each subject is electronically coded and identified by; sex (male or female), intensity of activity (Sedentary, Walking, or Very Active), and whether they are a Child, Teen, Adult or Senior. For this study, given all the subjects will be children, the third battery of coding (Child, Teen, Adult or Senior) will be changed to detect whether the student is Unprotected (no hat), Partially-Protected (wearing a baseball cap), Fully-Protected (wearing a 360 degree brim; broad-brimmed or bucket hat) or Fully-Protected (wearing a peak cap with back flap; legionnaire hat).

Separate scans are made for females and males, and simultaneous entries are also made for time of day, temperature, UV radiation level, area accessibility, area usability and presence of supervision. Each observation is conducted twice during the recess and lunch breaks for both females and males. This results in each school having 24 observations conducted at each data collection period (i.e. baseline, post-test and follow-up).

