Direct observations will be made in designated Target Areas that represent all standard locations likely to provide opportunities for students to have sun exposure during their recess and lunch periods (e.g. play equipment or outdoor sporting fields/courts). These Target Areas (one shaded and one non-shaded) will be predetermined and identified for observations prior to baseline assessments. A map will be provided to identify Target Areas and a standard observation order established for each school. Additional Target Areas may be added by observers on site and then documented.

During occasions of high student density, Target Areas will be subdivided into smaller Scan Spaces so that accurate measures can be obtained. Observers will use standard court or field markings to determine appropriate Scan Spaces within each Target Area. Data from these smaller spaces will be summed to provide an overall measure for each Target Area. A decision to subdivide a Target Area depends upon the (1) number of students in the area and (2) the type of student activity.

Additional data recorded prior to the direct observation scans includes;

1. Temperature and UV level at the start and end of the observation period; 2. Whether the observation was made at recess or lunch; 3. Start and finish times of recess and lunch; and 4. The condition of the target area. This is coded as follows:

A = Area is accessible (e.g. not locked or rented to others).

U = Area is usable for activity (e.g. is not excessively wet or windy).

SS = Area is supervised by designated school personnel who are role modelling sun safe behaviour (e.g. wearing a broad brimmed hat, wearing a shirt with a collar and minimum short sleeves, sunglasses, using shade).

SN = Area is supervised by designated school personnel who are not role modelling sun safe behaviour.

O = Organised physical activity (i.e. scheduled, with leadership by school personnel apparent) is occurring in the area (e.g. intramurals, interscholastic practices, fitness stations).

E = Equipment provided by the school or other agency is present (e.g. balls, jump ropes). This will not be coded as present if the only equipment is permanent (e.g. basketball hoops).

C = Covered area (e.g. the activity is taking place in an area where at least 50% of the target area is covered with shade provided by a permanent or natural feature such as shade cloth or tree foliage).

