Researchers will record whether the teacher supervising activities in the Target Area is role-modelling sun protective behaviour. An observation note will be added to the final iSOPARC data on whether the teacher is wearing a) a hat (broad brimmed or baseball cap), b) sunglasses or other appropriate eye protection (i.e. transition lensed optical glasses, and c) a sleeved shirt and collar.

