### Wearing of sunscreen

The secondary outcome will be children’s wearing of sunscreen during the school day. Currently no direct observation instruments to record the wearing of sunscreen exist. As a proxy measure of children wearing sunscreen, Grade 6 classes in control and intervention schools will be provided with one-litre containers of sunscreen for each class free of charge. Sunscreen will delivered to, and be collected from schools on the same day in order to ensure the period of use is the same in all schools; 50 days (10 school weeks) per interval. Each of the containers will their have branding removed but maintain their active ingredient information as required by the Therapeutic Goods Administration (TGA) [21]. A laminated instruction card will be attached to each bottle requesting classroom teachers to use the sunscreen as they normally would with their students.

The consumption of sunscreen from these containers will be recorded at the conclusion of the baseline, post-test and follow-up phases and will be replaced with full containers when they reach approximately 100 mL of sunscreen or less remaining.

In order to determine sunscreen consumption, 20 similar pump packs of sunscreen will be weighed to record an average starting weight for comparison. Consumption will then be analysed at the end of each data collection phase by comparing the net weight loss each pump pack of sunscreen issued to each school and the student number enrolled in Grade 6 classes who were issued the sunscreen.

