### Statistical methods

Statistical analysis of the primary and secondary outcomes will be conducted with linear mixed models using SPSS statistics version 20 (IBM SPSS Statistics, 2012) and alpha levels will be set at *p* > 0.05.

The models will be used to assess the impact of treatment (SunSmart Policy Intervention or Control), time (baseline, post-test and follow-up) and the group-by-time interaction, these three terms forming the base model. The models will be specified to adjust for the clustered nature of the data and will include all randomised participants in the analysis. Mixed models are robust to the biases of missing data and provide appropriate balance of Type 1 and Type 2 errors [22]. Mixed model analyses are consistent with the intention-to-treat principle, assuming the data are missing at random [23]. Sex, temperature/UV, time of day, type of period (recess or lunch) and conditions of target area (as previously outlined) will be included as covariates in the models.

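### Staff role modelling is counted among three study outcomes in one section, but the outcome and analysis sections rank only hats and sunscreen and use role modelling as a covariate

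*Protocol article*

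**What the plan says.** The Intervention design section says that the focus groups and interviews will examine each school's "utilisation of sun-safe hats, sunscreen and staff role modelling of sun-safe behaviours". Its next paragraph turns to other parts of school policy, such as uniforms, shade, scheduling and curriculum, and adds: "This broader context will allow analysis of the relative importance of the three specific study outcomes". The abstract places teachers beside students as subjects of observation: "Researchers will conduct three direct observations to record students’ hat use and teachers’ use of sun protective measures during recess and lunch periods".

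The outcome sections give two ranks. For headwear: "The primary outcome will be children’s wearing of a sun protective headwear during break periods of the school day". For sunscreen, in the singular: "The secondary outcome will be children’s wearing of sunscreen during the school day". Role modelling is measured in the headwear section in two ways. One is a pair of target-area codes, SS and SN, of which the first reads "SS = Area is supervised by designated school personnel who are role modelling sun safe behaviour". The other is a note on the teacher's clothing and eye protection: "Researchers will record whether the teacher supervising activities in the Target Area is role-modelling sun protective behaviour". Neither is given a rank.

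The Statistical methods section begins: "Statistical analysis of the primary and secondary outcomes will be conducted with linear mixed models". It then enters the target-area conditions, which include SS/SN, as covariates. The Discussion also lists teacher role modelling among the covariates.

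**The concern.** One variable has two roles: an outcome in the Intervention design section, and an adjustment term in the Statistical methods section and the Discussion. The document does not say which is meant.

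This matters because teacher behaviour is part of what the program tries to change. The Background names role modelling as a practice with room for improvement. The Discussion presents the direct observation of teachers as well as children as a feature of the evaluation, and says the design helps separate a poorly designed intervention from a poorly delivered one. A between-arm estimate for teachers would bear directly on that. Without a stated rank, definition and model, a teacher result could be promoted or left out after the data are seen.

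**Working it through.** **Outcome count, section by section (protocol article)**

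| Section | Hats | Sunscreen | Staff role modelling |
|---|---|---|---|
| Abstract, Methods/Design | observed | volume recorded | observed |
| Sample size calculation | basis of the calculation | not used | not used |
| Intervention design | study outcome | study outcome | study outcome |
| Wearing of headwear | primary | – | recorded (SS/SN and note), no rank |
| Wearing of sunscreen | – | secondary | – |
| Statistical methods | modelled | modelled | covariate, through target-area conditions |
| Discussion | – | – | listed as a covariate |

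The Intervention design sentence does not itself list its three outcomes. They come from the paragraph before it, which names exactly three items and is followed by a contrast with other policy aspects. The Background picks out the same three. No other set of three in the article fits.

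The counts are therefore three outcomes in one section, two ranked in the outcome sections and two modelled. The base model terms (treatment, time and their interaction) are specified for hats and sunscreen, not for role modelling. The article states no figure on this point, so there is none to reproduce.

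**Precision of an added role-modelling comparison at one wave**

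Inputs from the article: 5 intervention and 15 control schools (Recruitment and study participants), and 24 observations per school per wave (headwear section). The 24 is matched by 3 observation occasions × 2 breaks × 2 rounds × 2 sexes. That gives 5 × 24 = 120 intervention and 15 × 24 = 360 control observations per wave, which are upper limits for teacher data because scans can share a supervisor or have none.

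Assumptions not in the article: half of supervised observations are sun-safe (p = 0.5), intraclass correlation ρ is 0.05 to 0.20, and every observation is supervised. The number of distinct supervisor observations per school, m, is 12 if male and female scans share a supervisor (24 / 2). It is 6 if the two rounds within a break share one as well (24 / 4).

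SE = √[p(1 − p) × (ρ + (1 − ρ)/m) × (1/5 + 1/15)], with p(1 − p) = 0.25 and 1/5 + 1/15 = 0.2667. The 95% half-width uses t on 18 df (20 schools − 2), about 2.10.

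| m | ρ | ρ + (1 − ρ)/m | SE | 95% half-width |
|---|---|---|---|---|
| 12 | 0.05 | 0.129 | 0.093 | 0.195 |
| 12 | 0.10 | 0.175 | 0.108 | 0.227 |
| 12 | 0.20 | 0.267 | 0.133 | 0.280 |
| 6 | 0.05 | 0.208 | 0.118 | 0.248 |
| 6 | 0.20 | 0.333 | 0.149 | 0.313 |

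The interval would be about ±20 to ±31 percentage points, and wider if some observations are unsupervised.

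**The case against.** The strongest reply is that the rest of the article is consistent: hats primary, sunscreen secondary, role modelling a covariate. The sample size is built on headwear, the stated primary aim concerns children, and the Discussion calls role modelling a covariate outright. On this view the outlier is one loosely worded sentence about formative interviews, and changing one word there would settle it. This stands in part. Correcting the count is a legitimate repair, and the choice belongs to the sponsor. It does not remove the need to choose, because the article both calls the behaviour an outcome and records it in both arms at all three waves.

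A reader might infer more: that the trial can say nothing about teachers, that any later teacher result must be unplanned, or that a null hat result could not be interpreted. The document does not support these readings. The headwear section does describe how role modelling is recorded, so the data will exist and can be tabulated by arm. The full protocol and any SAP are not shown and could contain an analysis. What an SAP cannot do is make the article's sections agree with each other.

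The precision figures rest on assumed inputs. They describe the cost of adding the analysis and are not evidence of a defect.

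**Conclusion.** The inconsistency holds on the text. One section treats staff role modelling as a third study outcome. The outcome sections rank two others, and the Statistical methods section and the Discussion use role modelling only as a covariate. No analysis stated in the article has it as the dependent variable.

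The identification of the three outcomes rests on adjacent paragraphs of the Intervention design section and is the only reading that fits. The outcome-count mismatch leaves the primary and secondary estimates unaffected. The point should be corrected but is not critical. It is more than a wording slip because the behaviour is an intended target of the program, is already measured, and lacks only a rank, a definition and a model.

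**What to change.** Reconcile the Intervention design, outcome, Statistical methods and Discussion sections in one of two ways.

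**If role modelling is an outcome:**
- Name it as an additional secondary outcome, defined as the proportion of supervised observations coded SS rather than SN. Report unsupervised observations by arm.
- Make the two descriptions in the headwear section agree on which hats count. The SS code gives a broad-brimmed hat as its example, while the teacher note also accepts a baseball cap.
- Analyse it with a binomial mixed model with treatment, time, treatment-by-time and a school random effect, without counting the same supervisor more than once within a break.
- Remove SS/SN from the covariates of the main hat-effect model. At post-test and follow-up it is measured after randomisation and is targeted by the intervention, so adjusting for it could remove part of the effect on hats. Leaving it there would also make one variable both an outcome and an adjustment term.

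**If it is not an outcome:** correct the count of three in the Intervention design section and make no claim about an intervention effect on teachers.

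The first route costs one more pre-specified model on data already being collected, and one more secondary comparison with the wide interval shown above. The second costs a text correction.

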### Outcomes

Evaluation of the SunSmart Policy Intervention will involve a variety of instruments to report on sun protection behaviours that occur in primary schools. Trained research assistants who will be blind to the control or intervention allocation of the schools will conduct all assessments. All sun protection behaviour practices will be measured at baseline, post-test (12 months), and follow-up (15 months).

### Wearing of headwear and prevailing environmental conditions

The primary outcome will be children’s wearing of a sun protective headwear during break periods of the school day (i.e. recess and lunch). Currently no direct observation instruments to record sun-safe behaviours of children in school settings exist. However several direct observation tools of physical activity do exist, and one of these will be adapted to capture sun-safe behaviour data in children. The System for Observing Play and Recreation in Communities (SOPARC) is based on momentary time sampling techniques in which systematic and periodic scans of individuals and contextual factors within predetermined target areas are made [20]. iPad tablets (Apple Inc, USA) installed with the iSOPARC Application Version 1.75 (CIAFEL, Portugal: http://ciafel.fade.up.pt) will be used to provide an objective measure of the wearing of hats by children during recess and lunch.

During a scan each subject is electronically coded and identified by; sex (male or female), intensity of activity (Sedentary, Walking, or Very Active), and whether they are a Child, Teen, Adult or Senior. For this study, given all the subjects will be children, the third battery of coding (Child, Teen, Adult or Senior) will be changed to detect whether the student is Unprotected (no hat), Partially-Protected (wearing a baseball cap), Fully-Protected (wearing a 360 degree brim; broad-brimmed or bucket hat) or Fully-Protected (wearing a peak cap with back flap; legionnaire hat).

Separate scans are made for females and males, and simultaneous entries are also made for time of day, temperature, UV radiation level, area accessibility, area usability and presence of supervision. Each observation is conducted twice during the recess and lunch breaks for both females and males. This results in each school having 24 observations conducted at each data collection period (i.e. baseline, post-test and follow-up).

Direct observations will be made in designated Target Areas that represent all standard locations likely to provide opportunities for students to have sun exposure during their recess and lunch periods (e.g. play equipment or outdoor sporting fields/courts). These Target Areas (one shaded and one non-shaded) will be predetermined and identified for observations prior to baseline assessments. A map will be provided to identify Target Areas and a standard observation order established for each school. Additional Target Areas may be added by observers on site and then documented.

During occasions of high student density, Target Areas will be subdivided into smaller Scan Spaces so that accurate measures can be obtained. Observers will use standard court or field markings to determine appropriate Scan Spaces within each Target Area. Data from these smaller spaces will be summed to provide an overall measure for each Target Area. A decision to subdivide a Target Area depends upon the (1) number of students in the area and (2) the type of student activity.

Additional data recorded prior to the direct observation scans includes;

1. Temperature and UV level at the start and end of the observation period; 2. Whether the observation was made at recess or lunch; 3. Start and finish times of recess and lunch; and 4. The condition of the target area. This is coded as follows:

A = Area is accessible (e.g. not locked or rented to others).

U = Area is usable for activity (e.g. is not excessively wet or windy).

SS = Area is supervised by designated school personnel who are role modelling sun safe behaviour (e.g. wearing a broad brimmed hat, wearing a shirt with a collar and minimum short sleeves, sunglasses, using shade).

SN = Area is supervised by designated school personnel who are not role modelling sun safe behaviour.

O = Organised physical activity (i.e. scheduled, with leadership by school personnel apparent) is occurring in the area (e.g. intramurals, interscholastic practices, fitness stations).

E = Equipment provided by the school or other agency is present (e.g. balls, jump ropes). This will not be coded as present if the only equipment is permanent (e.g. basketball hoops).

C = Covered area (e.g. the activity is taking place in an area where at least 50% of the target area is covered with shade provided by a permanent or natural feature such as shade cloth or tree foliage).

Researchers will record whether the teacher supervising activities in the Target Area is role-modelling sun protective behaviour. An observation note will be added to the final iSOPARC data on whether the teacher is wearing a) a hat (broad brimmed or baseball cap), b) sunglasses or other appropriate eye protection (i.e. transition lensed optical glasses, and c) a sleeved shirt and collar.

